## Abstract

**Background:**

A Transient Ischaemic Attack (TIA) bears a high risk of a subsequent ischaemic stroke. Adequate diagnosis of a TIA should be followed immediately by the start of appropriate preventive therapy, including antiplatelets. The diagnosis of a TIA based on symptoms and signs only is notoriously difficult and biomarkers of brain ischaemia might improve the recognition, and target management and prognosis of TIA patients. Our aim is to quantify the added diagnostic value of serum biomarkers of brain ischaemia in patients suspected of TIA.

**Methods/design:**

Study design: a cross-sectional diagnostic accuracy study with an additional six month follow-up period.

Study population: 350 patients suspected of TIA in the primary care setting.

Patients suspected of a TIA will be recruited by at least 200 general practitioners (GPs) in the catchment area of seven TIA outpatient clinics willing to participate in the study. In all patients a blood sample will be drawn as soon as possible after the patient has contacted the GP, but at least within 72 h after onset of symptoms. Participants will be referred by the GP to the regional TIA outpatient clinic for additional investigations, including brain imaging. The ‘definite’ diagnosis (reference standard) will be made by a panel consisting of three experienced neurologists who will use all available diagnostic information and the clinical information obtained during the outpatient clinic assessment, and a six month follow-up period. The diagnostic accuracy, and value in addition to signs and symptoms of candidate serum biomarkers will be assessed in terms of discrimination with C statistics, and calibration with plots.

We aim to include 350 suspected cases, with 250 patients with indeed definite TIA (or minor stroke) according to the panel.

**Discussion:**

We hope to find novel biomarkers that will enable a rapid and accurate diagnosis of TIA. This would largely improve the management and prognosis of such patients.

**Trial registration:**

ClinicalTrials.gov Identifier NCT01954329

## Background

Cerebrovascular disease is the second leading cause of death in Europe and a leading cause of long- term disability [1]. A Transient Ischaemic Attack (TIA) by definition does not result in permanent damage of brain tissue [2], but the risk of a subsequent ischaemic stroke is substantial, especially within the first 2 weeks. Moreover, high-resolution MRI of the brain showed that many TIAs should be regarded as a minor stroke by revealing small ischaemic lesions. About 5 % of TIA patients will have a major stroke within 48 h, and another 5 % within 3 months [3, 4]. Urgent treatment of TIA patients with preventive treatment reduced the risk of stroke within 3 months by up to 80 % in a non-experimental study. An absolute reduction in stroke incidence from 10.3 % to 2.1 % was observed with implementing urgent diagnostic assessment followed immediately by adequate treatment including antiplatelets, when compared to a historical cohort in the same hospital in the UK [5]. Therefore, early recognition of TIA is of great importance. Recent studies underline the fact that TIA is a medical emergency [6] and adequate antithrombotic treatment reduces disability and health care related costs [7]. However, a rapid start of treatment may be hampered by patient and physician delay, waiting time involved in referral to the TIA outpatient clinic, and difficulties in establishing the correct diagnosis.

Diagnosing TIA is notoriously difficult for physicians. It is primarily based on history taking, since symptoms and signs often have resolved by the time the patient consults a physician, typically a general practitioner (GP). Symptoms may be inadequately observed by the patient or eyewitnesses, and the history can be distorted by difficulties in recalling the event. It is often difficult for lay persons to narrate the experienced symptoms. Moreover, TIAs can have a non-specific presentation and the differential diagnosis is broad. Particularly TIAs that originate from the vertebrobasilar artery system are difficult to recognise and hard to distinguish from other more benign causes of symptoms like dizziness. Neuroimaging techniques such as CT and MRI scanning of the brain are not performed to confirm the diagnosis of TIA, but to rule out other cerebral diagnoses, including cerebral haemorrhage [8]. In patients referred to a TIA service by the GP in Western Europe, the diagnosis TIA is confirmed by the neurologist in about 70 % of cases [9–11]. Even among experienced neurologists, however, there is substantial interobserver disagreement in TIA diagnosis, with Cohen’s kappa statistics varying from 0.65 to 0.78 [11]*.*

A possible solution to the diagnostic difficulties in TIA would be a serum biomarker that can reliably detect (transient) brain ischaemia in an early phase after symptom onset. This would enable a more accurate diagnosis within a shorter time frame. Especially in the primary care setting, but also in the emergency department, such a test would be very useful when available, preferably as a point of care (POC) test.

Biomarkers could also provide valuable prognostic information. Some markers have already shown to be helpful in predicting the risk of an ischaemic stroke within 2 weeks. This could be useful to guide rapid referral to a neurologist and early initiation of intensive treatment of risk factors, including anticoagulation in patients with atrial fibrillation, and carotid endarterectomy in cases with clinically relevant narrowing of the carotid artery.

There is a growing list of biomarkers associated with different components of the ischaemic cascade in the brain. To be useful in the diagnosis of TIA, a biomarker should be sensitive to early ischaemia and specific for the brain [12–14]. The biomarker should preferably be released in blood immediately after the ischaemic event and remain detectable for several days because it is then also applicable to patients who have a substantial patient delay. Based on a systematic review of the literature we selected seven biomarkers that potentially meet these criteria and showed to have diagnostic potential (table 1). The selection of markers is not definite and will be updated prior to our actual measurements. Previous biomarker studies in the field of cerebral ischemia up to now mainly focused on major stroke and showed methodological limitations which we want to overcome in the present study. To our knowledge, this study, Markers in the Diagnosis of TIA (MIND-TIA), is the first to evaluate the value of serum biomarkers in patients suspected of TIA in addition to history taking.

**Table 1 Tab1:** Main characteristics of potential diagnostic biomarkers for TIA

Biomarker (abbreviation)	Full name	Main biological action	Main study reference
B-FABP	Brain-type fatty acid binding protein	Protein involved in the intracellular transport and oxidation of fatty acids, and membrane lipid trafficking, expressed in glial cells	Wunderlich, et al. [20]
H-FABP	Heart-type fatty acid binding protein	Protein involved in the intracellular transport and oxidation of fatty acids, and membrane lipid trafficking, expressed in myocardium but also in neuronal cell bodies in the central nervous system	Wunderlich, et al. [20]
PARK7	Parkinson protein 7	RNA binding protein regulatory subunit, protects neurons against oxidative stress and cell death	Allard, et al. [21]
NDKA	Nucleoside diphosphate kinase A	Enzyme catalysing transfer of phosphate groups between nucleoside tri-phosphates and nucleoside diphosphates (e.g. ATP to GDP), expressed in neurons	Allard, et al. [21]
UFDP	Ubiquitin fusion degradation protein 1	Enzyme in the pathway for degrading ubiquitin-protein conjugates, involved in protein degradation in cell damage	Allard, et al. [22]
NR2A/2B	N-Methyl-D-aspartate (NMDA) receptor subunits	Product of the proteolytic degradation of NMDA receptors (part of the ischaemic cascade in the brain)	Dambinova, et al. [23]
NR2A/2B Ab	N-Methyl-D-aspartate (NMDA) receptor antibodies	Antibodies to NMDA receptor fragments	Weismann, et al. [24]

This paper presents the MIND-TIA study protocol.

### Primary objective

▪To assess the added diagnostic value of serum biomarkers beyond symptoms and signs in patients suspected of TIA.

### Secondary objective

▪To assess the short-term prognostic value of serum biomarkers in patients with TIA.

## Methods/design

### Study design

A cross-sectional diagnostic accuracy study with an additional 6 months follow-up period. Participants are patients suspected of a TIA by their GP. In all participants we will perform a biomarker assessment (index test) and the ‘definite’ diagnosis of TIA will be determined by an expert panel diagnosis (reference standard). A panel of three neurologists will evaluate all available diagnostic information, including imaging of the brain and additional ‘diagnostic’ information that became available in the 6 months of follow-up after the ‘event’ (so called delayed verification).

### Study population and setting

The study population will consist of patients suspected of a new (not necessarily first) possible TIA by the GP. Patients are recruited within 72 h after symptom onset and either directly after their GP consultation or at the time they visit the TIA outpatient clinic after referral by the GP. We will use the following inclusion and exclusion criteria:

#### Inclusion criteria

▪Age 18 years and older.▪A new episode of symptoms or signs suspected of TIA for which the GP considers referral to the TIA outpatient clinic for further investigations to confirm or exclude TIA, or for additional treatment.▪A blood sample can be collected within 72 h after onset of symptoms.▪Written informed consent.

#### Exclusion criteria

▪Patients that still have active symptoms or signs at the time of recruitment (i.e. during consultation of the GP), and thus are suspected of an ongoing stroke.▪If valid history taking is impossible because of severe cognitive impairment or insufficient knowledge of the Dutch language.▪Patients with a life expectancy of less than 6 months.

We aim to include 350 patients suspected of TIA, targeting at 250 patients who show to have a definite diagnosis of TIA according to the panel. Following the sample size calculation below, we need at least 200 recruiting GPs in the catchment area of four to five hospitals with a TIA outpatient clinic to complete inclusion within 2 years. Geographically, the study region in the centre of the Netherlands contains around 900 GPs and seven TIA outpatient clinics.

### Recruitment and consent

Patients suspected of TIA will be recruited (not included) by the participating GP or at the time they visit the TIA outpatient clinic after GP referral. The GP or TIA outpatient clinic personnel will ask if the patient agrees to be contacted by the researcher by telephone to explain the study and discuss possible participation.

The researcher will check whether the patient is eligible and still willing to participate. If so, a home visit by a research nurse is arranged and after the patient has signed informed consent, he/she is included in the study and further study procedures are initiated.

### Outcome measures

#### Diagnosis of TIA

Main study endpoint is the diagnosis of TIA (or minor stroke). The expert panel classifies subjects into i) TIA, ii) minor (or even major) ischaemic stroke, or iii) other diagnoses (haemorrhagic cerebrovascular disease or non-cerebrovascular disease). In the analysis we will use a composite endpoint of TIA and minor ischaemic stroke.

### Study procedures

Our study design aims to mimic the routine diagnostic routing of TIA as much as possible, as is common for diagnostic studies. For study reasons, a research nurse will visit the participant at home to draw an extra blood sample as soon as possible after inclusion for assessment of the biomarkers. After blood sampling participants complete a health-related questionnaire and the research nurse will fill out a standardised case record form (CRF) with items on history taking.

Following routine care, the GP will refer participants to the regional TIA outpatient clinic for further investigations and (additional) treatment. The neurologist will determine, in accordance with common practice, which additional tests should be performed. In the Netherlands the diagnostic evaluation at TIA outpatient clinics is organized according to national guidelines and is similar among hospitals. Brain imaging is performed in all patients suspected of TIA/minor stroke at the TIA outpatient clinics, nearly always CT scanning but increasingly next to this also MRI.

We will collect data on the following tests/assessments:The findings during medical history taking and the physical examination by the GP. This will be done retrospectively when patients are included.Venous blood sampling (20 ml of blood) for assessment of a set of biomarkers blinded to other results.Case record form (CRF) with standardised history taking, completed by the research nurse and including a narrative account back-upped on tape of the signs and symptoms by the patient.Findings during the clinical assessment of the neurologist at the TIA outpatient clinic, including electrocardiography, and if performed, carotid duplex scan and CT (or MRI) of the brain.Follow-up assessment of the six months following the event by scrutinising the electronical medical files of the participating GPs, with collection of data on all endpoints.

### Biomarker assessment

We will assess the levels of a set of biomarkers in a sample of blood taken within 72 h after onset of symptoms.

We will collect 20 ml of venous blood by venepuncture. The whole blood samples will be transported immediately to Saltro Diagnostic Center (an accredited primary care diagnostic facility in the Utrecht region) in a Cool Transport container. Pre-analytical processing will be performed within 3 h after collection. Serum will be separated by centrifugation at 2500 g for 10 min. The serum samples will then be stored in 0.5 ml aliquots at −80 °C and transported to the University Medical Center of Utrecht Biobank for long-term storage.

We plan to assess the following biomarkers by sandwich enzyme-linked immunosorbent assay (ELISA) procedures: B-FABP, H-FABP, PARK-7, NDKA, UFDP, NR2 and NR2Ab. These measurements will be performed at the end of the study in one single batch, and blinded to other results and outcomes.

The surplus of serum and a buffy coat will be stored to facilitate future (biomarker) investigations in (suspected) TIA patients.

### Panel diagnosis

An expert panel consisting of three neurologists will evaluate paper-based summaries of all case record forms (including medical history, initial signs and symptoms, the patient’s own narrative account of symptoms), reports of the neurologist, radiological imaging reports on brain imaging and carotid artery function, and six months of follow-up.

The panel will classify whether the patient has had a TIA, a minor (or even major) ischaemic stroke, or any other diagnosis. They will follow the definitions from the scientific statement of the American Heart Association ‘Definition and evaluation of TIA’ (2009) [2]. Within the group of TIA or minor strokes, the panel will also determine the aetiology of the ischaemic event, i.e. cardioembolic, large artery atherosclerotic, lacunar, other or undetermined aetiology. The panel judgement is made without knowledge of the biomarker values.

Every panel member will first assess the cases individually. Cases in which the panel members disagree will be discussed in a plenary meeting and a final decision will be made by voting, with the majority of votes counting. Panel meetings will be led by the researcher, who is responsible for providing all necessary data, but who will not participate in the consensus discussions.

Reproducibility of the panel diagnosis will be evaluated by calculating the inter-rater agreement with kappa statistics and by assessment of the reproducibility of the plenary decision process by reassessing a sample of around 10 % of the patients.

### Sample size calculation

Our sample size calculation is based on the primary research question to be able to answer whether any of the biomarkers has added diagnostic value beyond the clinical assessment. We applied Harrell’s rule of thumb [15] that may be used for power calculations in diagnostic and prognostic studies. This rule states that for every determinant considered for multivariate logistic regression analysis at least ten subjects are needed in the smallest category of the outcome variable.

On a TIA service the diagnosis of TIA is confirmed by the neurologist in around 70 % of patients referred by the GP [11, 16]. About 30 % of patients will be diagnosed as non-TIA (the latter being the smallest outcome category).

Following these proportions and because we evaluate up to 10 potential diagnostic determinants, 100 non-TIA patients are required. This means that we need a total of (100 x (1/0.3)=) 333 patients suspected of TIA. To be on the safe side and to allow for some ‘loss to follow-up’ and missing of essential endpoints, we aim to include 350 patients.

In case the proportion of non-TIA patients is higher than 30 %, less than 350 suspected TIA will suffice: we will stop inclusion after a total of 100 non-TIA patients have been verified by the panel and included in the study.

We realize that the power is insufficient for answering the secondary research question on prognosis based on an expected incidence of 20–30 follow-up events in six months. At the best, two or three predictors could be evaluated in multivariable regression analysis. The results on prognosis will therefore be hypothesis generating rather than hypothesis testing.

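### The early-stopping rule counts only panel-verified non-TIA patients, so it does not match the plan's smallest-category criterion, lags inclusion by six months and is not reconciled with the 250-case target

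*Protocol article*

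**What the plan says.** Protocol article, *Sample size calculation*. The size rests on a rule of thumb: for each determinant, "at least ten subjects are needed in the smallest category of the outcome variable". The plan then fixes which group that is: "About 30 % of patients will be diagnosed as non-TIA (the latter being the smallest outcome category"). From this it concludes that "because we evaluate up to 10 potential diagnostic determinants, 100 non-TIA patients are required" and "This means that we need a total of (100 x (1/0.3)=) 333 patients suspected of TIA", raised to 350 to allow for losses. The contingency follows: "In case the proportion of non-TIA patients is higher than 30 %, less than 350 suspected TIA will suffice", and "we will stop inclusion after a total of 100 non-TIA patients have been verified by the panel and included in the study". It gives no upper limit for the non-TIA share and no minimum for the TIA group.

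*Panel diagnosis* lists what the panel sees, ending with "radiological imaging reports on brain imaging and carotid artery function, and six months of follow-up". *Study design* calls this delayed verification. The article describes no provisional verdict that could feed the count.

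The text after the *Exclusion criteria* sets 350 suspected patients, "targeting at 250 patients who show to have a definite diagnosis of TIA according to the panel", with inclusion to be completed in two years. The Abstract gives the same 250, there counting minor stroke with TIA.

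**The concern.** Three things do not fit together.

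1. **Criterion and count.** The requirement is 100 in the smaller outcome group. The stop is tied to non-TIA, which is the smaller group only while its share is below 50%. The contingency exists for the case where the 30% assumption is wrong, yet it assumes that the order of the two groups cannot change.
2. **Timing.** A verdict that uses six months of follow-up cannot exist for patients enrolled in the last six months. The rule is offered as a way to include fewer patients, but for shares a little above 30% the sample would normally be complete before the count reaches 100.
3. **Target.** The plan states 250 definite cases in two places and does not say what happens to that number if inclusion stops early.

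At stake are a stopping decision that does not do what the text promises, an unguarded case group, and a stated target that an early stop must miss.

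**Working it through.** **Inputs.** Ten determinants, ten subjects each, 30% non-TIA, target 350 (*Sample size calculation*); two years of inclusion and 250 cases (text after *Exclusion criteria*); six months to verdict (*Study design*, *Panel diagnosis*). My assumptions: uniform accrual, a constant non-TIA share *p*, 350 as the ceiling, and no delay beyond six months for panel meetings. Any such delay lengthens the lag. *Cases* means TIA or minor ischaemic stroke.

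**The plan's own figure.** 10 × 10 / 0.30 = 333.3, which reproduces the stated 333. At 350 patients and 30% non-TIA, the expected split is 105 non-TIA and 245 cases.

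**Lag.** 350/24 = 14.58 per month; × 6 = 87.5 patients enrolled but not yet verifiable. When patient 350 enters, at most 350 − 87.5 = 262.5 can have a verdict. At 30% that is 262.5 × 0.30 = 78.8 verified non-TIA patients.

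**When the rule can act.** It needs 100 non-TIA among those 262.5, so *p* > 100/262.5 = 0.381. With 36-month accrual the lag is 58.3 and the threshold 0.343; with 18-month accrual they are 116.7 and 0.429. These are expected counts. The binomial probability of at least 100 non-TIA among the first 262 patients is 0.003 at 30%, 0.156 at 35%, 0.501 at 38%, 0.747 at 40% and 0.989 at 45%.

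**Numbers at the stop.** Without lag N = 100/*p*; with lag N = min(350, 100/*p* + 87.5). Cases = (1 − *p*) × N.

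| Non-TIA share | N, no lag | Cases, no lag | N, with lag | Cases, with lag | Cases if all 350 recruited |
|---|---|---|---|---|---|
| 30% | 333.3 | 233.3 | 350 | 245 | 245 |
| 35% | 285.7 | 185.7 | 350 | 227.5 | 227.5 |
| 40% | 250 | 150 | 337.5 | 202.5 | 210 |
| 50% | 200 | 100 | 287.5 | 143.8 | 175 |
| 55% | 181.8 | 81.8 | 269.3 | 121.2 | 157.5 |
| 60% | 166.7 | 66.7 | 254.2 | 101.7 | 140 |
| 65% | 153.8 | 53.8 | 241.3 | 84.5 | 122.5 |

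The saving at 40% is 350 − 337.5 = 12.5 patients, against 350 − 250 = 100 if verdicts were immediate. At 50% it is 62.5 against 150.

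**When cases fall below 100.** Without lag, 100/*p* − 100 < 100 gives *p* > 0.50. With lag, (100/*p* + 87.5)(1 − *p*) = 100 becomes 87.5*p*² + 112.5*p* − 100 = 0, so *p* = 0.605 (0.571 with 36-month accrual).

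**The 250 target.** This needs no assumption about lag. A stop before 350 with at least 100 non-TIA patients leaves fewer than 350 − 100 = 250 cases.

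**The case against.** The strongest reply is that waiting for the panel is the cautious choice. It ensures 100 non-TIA patients by the reference standard, and where the rule does not act, the study simply recruits its planned 350. That stands. The lag adds patients and costs efficiency only. Biomarkers are measured in one blinded batch at the end and the panel does not see them, so the count does not depend on the index test.

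A reader might infer more than the documents support:

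- **That cases could drop to 82 or 67 at 55% or 60% non-TIA.** Those figures assume immediate verdicts. With the lag they are about 121 and 102, above the plan's 100. The article expects about 30% non-TIA, and nothing in it suggests a non-TIA majority.
- **That the rule is what defeats the 250 target.** At 40% the full 350 would yield only 210 cases, against about 203 under the rule. The prevalence causes most of that miss. No calculation rests on 250; it is close to 70% of 350 (245). The contingency also openly allows a smaller total, so the two statements are unreconciled rather than flatly contradictory.
- **That precision is seriously damaged.** At an assumed sensitivity of 80%, the 95% half-width at 40% non-TIA is 1.96 × √(0.16/210) = 5.4 points with all 350 and 1.96 × √(0.16/202.5) = 5.5 points under the rule. At 50% it is 5.9 (175 cases) against 6.5 (143.8). The prognostic part is already declared hypothesis-generating.
- **That non-TIA literally includes minor strokes.** The Abstract, *Outcome measures* and *Data analysis* all pair TIA with minor stroke, so in context non-TIA is the complement of that composite.

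What remains is the missing guard on the smaller group, the overstated saving, and the silence on 250.

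**Conclusion.** The rule should be brought into line with the plan's own criterion and targets. On expected counts it cannot shorten inclusion unless the non-TIA share exceeds about 38% (34% to 43% for 36- to 18-month accrual), although by chance it may act somewhat below that. It leaves the case group unguarded, which bites only above about 60% non-TIA with the lag, or 50% without. Any early stop ends below 250 cases. The lag is an inefficiency and neither biases the analysis nor reduces precision. The thresholds rest on uniform accrual, a constant share and verdicts at exactly six months; the mismatch between criterion and count, and the arithmetic on 250, do not. Severity: minor to should-fix.

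**What to change.** Choose one of two options.

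1. Delete the early stop and recruit the planned 350.
2. Keep it, but stop early only when both analysis groups (TIA/minor ischaemic stroke, and other diagnoses) have at least 100 panel-verified patients. State that every included patient is analysed, including those still unverified at the stop, and acknowledge that the six-month lag limits the saving.

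In either case, restate 250 as the number expected at about 70% confirmed (245 of 350), and say that it lapses if the non-TIA share is higher or inclusion stops early.

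Option 2 changes nothing while non-TIA is at or below 50%. At 65% the case group would reach 100 verified only at 100/0.35 + 87.5 = 373, so recruitment would run to 350 and give 122.5 cases instead of 84.5.

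The cost is one paragraph of text and, at most, recruitment to the 350 already planned. Stopping on the clinic neurologist's diagnosis alone would remove most of the lag, but it is a trade-off. The Background reports kappa of 0.65 to 0.78 between neurologists, and inclusion could end with fewer than 100 panel-verified non-TIA patients.
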